### Physiological measures

- **Body composition**

At baseline, weeks 12 and 24, body weight will be collected (to the nearest 0.1 kg respectively). BMI will be calculated based on body weight and height. Bioelectrical Impedance Analysis (BIA) will be used to estimate body composition, including body fat percentage and lean body mass and fat mass.

- **Blood pressure (systolic and diastolic)**

At baseline, weeks 12 and 24, arterial blood pressure will be measured in the seated position using an automated sphygmomanometer after participants have been resting for ~5min. Three measurements will be obtained and the average of the last two measurements will be used.

- **Handgrip strength**

At baseline, weeks 12 and 24, handgrip strength will be measured using a handheld dynamometer three times on each side, with the elbow flexed at a right angle and the forearm in neutral position ^92^. The maximum of the readings generated is taken as the maximum grip strength.

### Physical function

- **Short Physical Performance Battery**

At baseline, weeks 12 and 24, the Short Physical Performance Battery (SPPB) will be used to objectively measure physical function. The SPPB measures balance, gait speed and ability to stand from a chair^93^. It comprises three tests outlined below, each scored out of 4 (for a maximum total score of 12) in accordance with available guidance:

- Chair sit-to-stand: The participant will start from a seated position on a hard, upright chair (such as a dining chair) of standardised height, with the feet flat on the floor and the knees bent at 90°. For the test, the time taken for the participant to stand up fully and then return to sitting 5 times without using the hands is measured.
- Standing balance: Static standing balance is tested in three progressive positions. If the participant can maintain the specified position for at least 10 seconds, then the position is progressed to the next stage:
  - Feet together
  - Semi-tandem
  - Tandem
- Gait speed: Gait speed is calculated from the time taken for the participant to walk 4 metres at their usual speed on a level course. It is measured twice with a short break in between, and the best score used.
- **Berg Balance Scale**

At baseline, weeks 12 and 24, the berg balance scale will be used to assess the participants balance^94^. The berg balance scale includes 14 tasks that are scored on a 5 point scale, with 0 as the lowest level of function and 4 as the highest^94^, with the total score being out of 56. The berg balance scale is a valid and reliable to assess balance^95^.

### Accelerometer and inclinometer measured physical behaviours

At baseline, weeks 12 and 24, we will aim to assess physical activity, sedentary behaviour and sleep parameters objectively using accelerometery worn for approximately 9 full days (24-hours per day) to capture 3-4 days with >10 hours of valid wear time^96^. Two devices (one wrist-worn, GeneActiv (accelerometer), on the non-dominant side, and the other, activPAL (inclinometer) placed on the thigh) will be worn. The GeneActiv will capture triaxial acceleration data and data will be processed using an open-source R programme (GGIR) according to SOPs developed for the NIHR Leicester Biomedical Research Centre^97^. Postural allocation (sitting and standing) and walking will be quantified using an activPAL physical activity monitor (PAL Technologies, Glasgow, Scotland). The activPAL is a single-unit monitor based on a triaxial accelerometer that is worn midline on the anterior aspect of the thigh and attached directly onto the skin using medical dressing. The monitor produces a signal related to thigh inclination and has been shown to be a valid and reliable measurement tool for determining posture during activities of daily living in a healthy population. Participants will be given a daily log sheet to record their sleep times each day and any times that they may have removed the monitor, to facilitate future analyses.

### Patient reported outcome measures (PROMS)

- **EuroQol-5 Dimensions (EQ-5D-5L)**

At baseline, weeks 12 and 24, self-reported quality of life will be assessed using the EQ-5D-5L questionnaire. The EQ-5D-5L is used as a standardised measure of self-reported health status and quality of life and is considered to have a good discriminatory power and validity. The EQ-5D-5L will be used to determine health state descriptions for five components combined with preference-weighted health-related quality of life index scores (as approved by NICE) to generate Quality Adjusted Life Year (QALY) profiles for the cost-effectiveness analysis^98^.

- **Short Form-36**

The Short Form 36 Health Survey Questionnaire (SF-36) is 36 item measure of health-related quality of life across multiple domains assessing functional status and wellbeing^99^. It has shown to be an acceptable, valid and reliable measure of measuring health-related quality of life. The questionnaire will be scored in accordance with available guidance.

- **Late Life Function and Disability Instrument (Late-life FDI)**

At baseline, weeks 12 and 24, the late-life function and disability instrument (late-life FDI) will be used to assess changes in function and disability^100^. The late-life FDI is split into disability that looks at socially defined tasks and functions that involves activities of daily living^101^. The disability section is 16 items and each question should be rated on a scale of 5-1 for a) frequency (i.e. “how often…”) and b) limitation (i.e. “to what extent do you feel limited in…”)^101^. The function section is 32 items and each question is rated on a scale of 5-1 ^101^.

- **Patient Outcome Scale (POS)**

At baseline, weeks 12 and 24, the Patient Outcome Scale (POS) will be used to measure the physical symptoms, psychology, emotional, spiritual information and support needed for people with long term conditions^102^. The POS is a widely used, multidimensional, 11 item assessment of quality of life for people with long term conditions^102^. The answers are on a 5 point Likert scale (aside from question 9 which has 3 points and an open question around main problems experienced by participants)^102^. The total score is out of 40, with 0 indicating a better quality of life and 40 indicating a lower quality of life^102^.

- **Goal Attainment Scale (GAS)**

At baseline, weeks 12 and 24, the goal attainment scale (GAS) will be completed by participants.  GAS is a way to measure to what extent participants' goals have been achieved during the intervention on a standardised 5-point scale and converted to a T-score to provide a single figure that reflects the overall extent of achievement and allows for analysis.^103^. The GAS is widely used in healthcare, including areas such as rehabilitation, physical therapy and care in an older populations ^103^.

- **Zarit Burden Interview (carers only)**

At baseline, weeks 12 and 24, the Zarit Burden interview will be used for carers only. The Zarit burden interview is a 22 item questionnaire used to assess carers perceived burden of providing care using a 5 point Likert scale  ^104^. Scores are added up (out of 88), with higher scores suggesting greater burden  ^104^. The Zarit burden interview is one of the most used measures of burden and is a valid and reliable instrument to measure carer burden ^104^.

## Mixed methods process evaluation

An embedded mixed methods process evaluation, combining relevant data gathered from multiple sources will be conducted according to the NIHR/ Medical Research Council guidelines^89, 105.^ Normalisation Process Theory (NPT) will provide an additional sensitising framework for data collection and analyses of the interviews^106, 107^. Further information about NPT is provided in section 7.7.

The process evaluation will focus on the following priority areas which have been identified by the research team as areas of greatest importance ^89^:

**1.Intervention:**

**Implementation**

Assessments of implementation will include establishing:

- Fidelity
  - Whether the key functions of the intervention were delivered as intended according to the fidelity checklist
  - The quality of intervention delivery according to the fidelity checklist and questionnaire data (see section 7.3.2)
- Dose
  - The number of reviews attended
  - The number of physical activity officer sessions attended (where applicable)
  - The number of community groups sessions attended (where applicable)
- Reach
  - Whether the intended audience encounters the intervention, and how

**Mechanisms of impact**

Potential mechanisms of intervention effectiveness and of participant engagement with the intervention

**Context**

How contextual factors influenced intervention adoption and impact, including any unintended consequences.

**Acceptability**

**Including:**

- - exploration of the influence of interaction between participants who took part as a ‘dyad’
  - The inclusion of physical activity officer support and engagement with community groups, where this has been possible.
  - barriers and facilitators to engagement

**2 Trial:**

The acceptability of key trial procedures, outcome measures and exploration of any unintended harms and consequences

These methods used to address these areas (including quantitative intervention process data described earlier in section 7.1.1), and with which stakeholder groups are outlined in Table 2.

Table 2. Methods used within the process evaluation.

| **COMPONENT** | **IMPLEMENTATION** | | | **MECHANISM OF IMPACT** | **CONTEXT** | | **INTERVENTION ACCEPTABILITY** | | **TRIAL ACCEPTABILITY** |
| --- | --- | --- | --- | --- | --- | --- | --- | --- | --- |
| **PARTICIPANTS** |  | HCPs* | Participants | Participants♯ | HCPs* | Participants♯ | HCPs* | Participants♯ | Participants♯ |
| **METHODS AND DATA COLLECTED** | Fidelity | - Audio recording of sessions and Fidelity checklist - SDM questionnaire data from the intervention group | Engagement/ adherence process data^+^ | Interview | - Interview - Site contextual information | Interview | Interview | - Interview - Engagement/ adherence data^+^ - 24 hour physical behaviours questionnaire | Interview |
|  | Dose | Process data on number of:   - reviews - physical activity officer sessions - community groups   attended | Engagement/ adherence process data^+^ | Secondary outcome data** |  |  |  |  |  |
|  | Reach | Process data on:   - characteristics of participants receiving the intervention - completers and non-completers - those with high engagement vs low engagement^+^ | |  |  |  |  |  |  |

Abbreviations: HCP, health and care professionals; SDM-Q-9, 9-Item Shared Decision-Making Questionnaire. *’HCP’ refers to those providers who are involved in the intervention delivery, including physical activity officers and community providers. ** secondary outcome data is detailed in section 7.2. ^+^ Engagement and adherence data is detailed in section 7.1.2. ♯ ‘Participants’ refers to people living with MLTC and frailty and carers with the intervention group (see section 7.3.1) and includes those who have withdrawn voluntarily.

### Participant eligibility criteria for the mixed-methods process evaluation

Participants and their carers who are enrolled in the trial and randomised to the intervention arm will be eligible to participate in the process evaluation. Those who voluntarily withdrew, but not those who were withdrawn for reasons of ill-health, illness, injury, progression of disease etc, from the intervention will remain eligible for interview.

Health and care professionals (defined as physical activity officers and other link or community workers who are involved in the delivery of the physical activity officer components of the PERSONAL-AGILITY intervention, or the local community groups that participants choose to attend as part of the intervention) will also be eligible provided, they are:

- Clinical and non-clinical staff delivering the PERSONAL-AGILITY study or community-based sessions the participant has accessed as part of the intervention.
- Aged ≥ 18 years
- Able to provide written informed consent

### Data collection

In addition to the quantitative acceptability data outlined in section 7.1.3, quantitative process data will include assessment of intervention fidelity. Due to the feasibility nature of this study, the intervention (apart from the physical activity officer sessions which will be delivered by the physical activity officers and community providers) will be delivered by the research team. Given that the intervention:

- Is complex and targets multiple behaviours (sleep, physical activity and sedentary behaviour) which are selected by the participants in line with a shared decision-making approach
- Can include both carers and people with MLTCs in a ‘dyad’

an assessment of intervention fidelity for those sessions provided by the research team will still provide useful data that will inform the future implementation of the intervention within a definitive trial and to refine a training package for intervention providers within this definitive trial.

Informed consent to audio record PERSONAL-AGILITY sessions will be sought from all participants. Audio-recording all sessions is the current gold standard for intervention fidelity assessment^108^. The fidelity assessment will be completed using audio recorded sessions and a fidelity checklist and coding manual developed by the study team. and will be undertaken by trained observers. This checklist and manual will be developed *a priori* by two researchers to ensure it accurately reflects the PERSONAL-AGILITY intervention, but will include the following areas:

- Duration and focus of the intervention
- Intervention providers’ behaviours consistent with a shared decision-making approach
- Behaviour change techniques used as intended
- Key messages, or content of the intervention is delivered as intended
- Digital tools and other resources and materials used as intended
- Adaptations made to the intervention

Where possible, two people will undertake the fidelity assessments and inter-rater reliability assessed. Once agreement is established, intervention fidelity assessments may be carried out by one researcher.

All sessions will be audio-recorded with audio-recordings from initial and follow-up assessments, physical activity officer sessions (where applicable) and follow-up phone calls included. Around 10% of the programme delivered will be analysed, which is consistent with recommendations within the literature ^108^.

Sessions analysed will purposively include a mixture of early (after the first six months of recruitment) mid (midway through recruitment) and late sessions (within the last six months of the study) as per the qualitative interviews (see section 7.7), from across the duration of the study to account for intervention provider practice effects. This will also account for the fact that emerging results from the process evaluation will be used to iteratively improve delivery of the intervention and the study, so fidelity may vary over time for this reason^89^.

In addition to the fidelity assessments, at weeks 12 and 24, the 9-item shared decision-making questionnaire (SDM-Q-9) will be completed by participants within the intervention group. The questionnaire is used to assess the HCP and participant behaviours during decision making using a 6-point Likert scale ranging from “completely disagree” to “completely agree” in response to statements such as: “My doctor explained the advantages and disadvantages of the treatment options”^109^. The 9-item shared decision making questionnaire has good reliability, validity and feasibility ^109^.

Information on dose and reach of the intervention will be gathered from intervention records and participant characteristics from the trial. Local authority profile questionnaires, informed by the Context and Implementation of Complex Interventions (CICI) framework, will be collected to provide contextual information for each area and situate the analysis and interpretation of findings; these will contribute to better understanding the context in which the intervention is delivered. An initial outline for the profile questionnaire is included in Appendix C.

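### The early window for fidelity scoring opens only after six months of recruitment, so on its words the start-up sessions, where provider practice effects are likely largest, are never sampled

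*Protocol*

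**What the plan says.** Section 7.3.2 of the protocol (Data collection) describes the fidelity check.

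- **Recording.** "All sessions will be audio-recorded with audio-recordings from initial and follow-up assessments", physical activity officer sessions and follow-up calls included. Consent to record is sought from all participants.
- **Amount scored.** "Around 10% of the programme delivered will be analysed".
- **Choice of sessions.** "Sessions analysed will purposively include a mixture of early (after the first six months of recruitment) mid (midway through recruitment) and late sessions". The late window is "within the last six months of the study) as per the qualitative interviews (see section 7.7").
- **Purpose of the spread.** Sessions come "from across the duration of the study to account for intervention provider practice effects". The section adds that fidelity may change because emerging findings will be used to improve delivery.
- **Who delivers.** The research team, except for physical activity officer sessions, which fall to the officers and to community providers.
- **Who scores.** The tool is "a fidelity checklist and coding manual developed by the study team", and the assessment "will be undertaken by trained observers". Two people assess where possible until agreement is established; after that, one may suffice.

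The section does not say who selects the recordings or how they are chosen within a window. Section 9.6.1 summarises the observation data descriptively. Section 7.3.2 says the fidelity results are to inform implementation and a provider training package for the definitive trial.

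**The concern.** The sampling rule and its stated purpose do not fit each other. Practice effects are likely to be strongest when providers first deliver the intervention, yet the earliest window opens only once six months of recruitment have passed. On the words of the sentence, the first sessions have no window from which to be drawn.

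Those sessions also precede the first planned refinement. The first interview round (section 7.7) falls after six months and looks for initial problems, and section 9.6.2 uses the qualitative findings to refine the intervention as the study runs. If no earlier delivery is scored, fidelity before and after that first round cannot be compared.

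What is at stake is the meaning of the fidelity summary. It would describe delivery by providers who already have some practice, although its main stated use is to design training for new ones.

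**Working it through.** **1. Where the window comes from.** Section 7.3.2 takes its time points from section 7.7. There, participant interviews take place after the 24-week visit or at withdrawal, so apart from early withdrawals none can occur in roughly the first five and a half months. Recordings exist from the first session. The reason for a late start holds for interviews and not for recordings.

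**2. Inputs.**
- 50 people with multiple long-term conditions and frailty, allocated 2:1 (section 3): 50 × 2/3 ≈ 33 in the intervention group.
- Intervention and follow-up of 24 weeks: 168/30.44 = 5.52 months.
- Planned trial period 36 months (Trial Summary). The study ends 12 months after the last 24-week visit (section 7.10).
- Recruitment length R is not stated. If the 36 months include the 12-month close-out, R is at most 36 − 12 − 5.52 ≈ 18.5 months.

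**3. How much lies before month six.** Assume uniform accrual over R months and delivery spread evenly over 5.52 months per person.
- Share of participants recruited before month six = 6/R.
- Share of delivery time before month six: people recruited in the first 0.48 months (6 − 5.52) complete everything before month six, and those recruited from 0.48 to 6 months complete on average half. The share is (0.48 + 5.52/2)/R = 3.24/R.

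**4. Possible effect on the summary.** Assume fidelity of 60% before month six and 80% after. Omitting the early part overstates the overall figure by 20 points × the omitted share. For initial sessions, which take place close to recruitment, that share is 6/R.

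| R (months) | Recruited before month 6 (of 33) | Delivery time before month 6 | Overstatement, all delivery | Overstatement, initial sessions | Midpoint of recruitment (month) |
|---|---|---|---|---|---|
| 9 | 67% (22) | 36% | 7.2 points | 13.3 points | 4.5 |
| 12 | 50% (17) | 27% | 5.4 points | 10.0 points | 6 |
| 15 | 40% (13) | 22% | 4.3 points | 8.0 points | 7.5 |
| 18 | 33% (11) | 18% | 3.6 points | 6.7 points | 9 |

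With a smaller assumed contrast (70% then 80%), the overstatement halves. If R is 12, the early and mid points coincide at month six. If R is 9, the mid point precedes the early one and reaches part of the start-up period, so that row is an upper limit. The wording works as an ordered sequence only when recruitment lasts longer than 12 months.

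**5. The late window.** The study ends 12 months after the last 24-week visit, so its last six months run from 6 to 12 months after that visit. If sessions finish by week 24, the late window contains none.

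**6. Number scored.** Sessions per person are not stated. At an assumed 3 to 12 each, there are about 100 to 400 sessions (33.3 × 3 to 33.3 × 12), of which 10% is 10 to 40, or about 3 to 13 per window.

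**The case against.** The strongest reply is that the six-month mark may be the time at which a first batch of recordings is reviewed, as section 7.7 uses it for interviews. On that reading the first batch could include start-up sessions, and the stated intention to sample across the whole study supports it. The reading is possible, but the sentence applies the label to the sessions analysed and not to a review date. The wording needs correcting under either reading.

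A reader might go further and infer that the research team, which delivers most of the sessions, also picks the ones to be scored, and that fidelity will therefore look too good. The protocol does not support this. It names no selector. Its purposive wording describes spread over time and not choice by quality. Trained observers score against a checklist and manual written in advance, and the recordings include physical activity officer sessions that the research team does not deliver. What stands is narrower: no rule for choice within a window is given, and neither selectors nor raters are stated to be separate from deliverers. Selection bias is a possible risk and has not been shown.

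The reply is also right on impact. Purposive sampling is legitimate in a descriptive process evaluation. Implementation in Table 5 (section 9.4) is judged by completion of reviews and not by a fidelity score, and the participant-completed shared decision-making questionnaire gives a second view of delivery.

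**Conclusion.** The point holds in a limited form. As worded, the early window leaves out start-up delivery, against the sentence's own purpose, because a time point suited to interviews was applied to recordings. The fidelity summary, and the training package it informs, may then not represent novice delivery.

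For recruitment of 12 to 18 months, the period before the early window covers 50% to 33% of intervention participants and 27% to 18% of delivery time. With an assumed rise in fidelity from 60% to 80%, the overall figure would be overstated by about 5 to 4 points, and that for initial sessions by 10 to 7. These sizes rest on uniform accrual, even delivery and an assumed learning effect. The protocol gives none of these, and the overstatement arises only if fidelity improves with practice. No progression decision depends directly on the score, so this is a correction worth making cheaply and not a threat to the trial.

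**What to change.** Rewrite the sampling paragraph in section 7.3.2:

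- Define early, mid and late as thirds of all delivered sessions in order of delivery, starting with the first session. This also ties late to the end of delivery instead of the end of the study.
- Draw about 10% at random within each third.
- Check that the main session types (initial, follow-up, physical activity officer, phone) are represented, without forcing a grid. Three thirds by four types makes 12 cells, too many if only 10 sessions are scored.
- Have the list generated by someone who did not deliver the sessions, where existing staff allow.

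The cost is one paragraph and a random list. All sessions are already to be recorded and the number scored is unchanged. The downside is slightly less freedom to hand-pick informative sessions.
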